### Study population

Participants are claimants for a disability pension according to the Dutch *Work and Income Act (WIA)*, which can be claimed after being sick-listed for 104 weeks. All disability claimants will be recruited in three different offices of the Dutch Workers Insurance Authority, UWV (Leiden, Den Haag, Rotterdam). UWV is responsible for evaluating disability claims in the Netherlands. Claimants will receive an invitational letter for the disability assessment including a study information brochure. The latter will direct claimants to an online application form. This application form includes questions concerning the study's in- and exclusion criteria and an informed consent. Recruitment will take place over a 8-month period (January 2009 – August 2009).

All insurance physicians from the participating UWV offices, and responsible for disability assessments concerning the Dutch *Work and Income Act (WIA)*, were asked to participate in the study.

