### Randomization

Randomization will be conducted at the individual claimant level. After baseline measurements, disability claimants will be randomized in either the intervention or control group. Randomization to these two groups will be done by block randomization. To prevent unequal groups, 3 blocks will be created (3 UWV offices). A computerized random number generator will draw up an allocation schedule for each block. In consequence of the nature of the intervention (interactive website vs. a 'sham' website with commonly available information), claimants will be blinded for study design. Insurance physicians will be aware of the study's design, but will not be informed about the allocation of disability claimants.

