**Figure 1 F1:**
[figure not shown]
**Overview of study procedures**.

In the Dutch social security system, workers that are long term sick-listed can apply for a disability benefit at approximately 91 weeks after the start of their sick leave. Around the 102^nd ^week of being sick-listed, these workers will receive an invitation from UWV to visit an insurance physician,. Together with this standard invitation from UWV, this study will send along an invitational letter and the study's information brochure. In this brochure, instructions are given on how to participate in the study by filling out an online application form. This online form includes questions concerning the study's in- and exclusion criteria and an informed consent. Subjects who meet all the criteria and are willing to participate in the research will be directed to the baseline questionnaire (T_0_). When subjects finish filling out the baseline questionnaire, they will be randomized in either the intervention group or control group. Disability claimants who are randomized into the intervention group, will receive an email with a username and password that gives them full access to the website intervention. Participants who are randomized into the control group receive an email that directs them to a website with commonly available information only. Before each follow-up measurement, subjects from both groups will receive emails in which they are asked to fill out the online questionnaires. Reminders will be sent to increase compliance.

Insurance physicians receive a newsletter with information about the ongoing of the project. Directly after a disability assessment with a claimant participating in the study, insurance physicians will be asked to fill out a short questionnaire, which they will receive by email.

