### Secondary outcomes

#### Claimants satisfaction

The satisfaction of claimants with their insurance physicians will be measured with the AStri questionnaire [48]. This questionnaire, which is specially designed to measure patient satisfaction in the field of insurance medicine, contains 29 items divided over six subscales, each representing a different component of patient-insurance physician interaction (Listening, Empathizing, Correctness, Clearness, Rigorousness, and Professionalism). Testing of this questionnaire resulted in a good internal consistency (all subscales had a Cronbach's alpha greater than 0.78) [48].

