### Statistical analysis

Baseline values will be analyzed for differences between the two groups, by one-way-analysis of variance for numerical data and chi-square for categorical data. The primary analysis will be a comparison of the change in empowerment between the intervention and control group following the "intention-to-treat" principle. On data from questionnaires filled out on more than one occasion (e.g. empowerment, coping strategy, knowledge) we will use a repeated measurement analysis to test if both research groups diverged from baseline to follow-up. With data that will be measured on one occasion (e.g. claimant satisfaction, insurance physicians satisfaction and perceived justice) we will use t-tests to detect possible differences between the two research groups. Additionally, a per-protocol analysis will be performed.

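### Plain t-tests on physician and claimant satisfaction leave physician and office variation in the error; a random physician intercept could sharpen both secondary comparisons at little cost

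*Protocol article*

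**What the plan says.** The Statistical analysis section of the Protocol article names the test for outcomes measured once: "With data that will be measured on one occasion (e.g. claimant satisfaction, insurance physicians satisfaction and perceived justice) we will use t-tests". No term for physician or office is mentioned.

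Four other places describe how these data arise.

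- **Study procedures** (text under Figure 1): "Directly after a disability assessment with a claimant participating in the study, insurance physicians will be asked to fill out a short questionnaire". The unit of a physician rating is therefore the assessment, not the physician.
- **Claimants satisfaction:** "The satisfaction of claimants with their insurance physicians will be measured with the AStri questionnaire". Claimants seen by the same physician rate the same person.
- **Study population:** "All insurance physicians from the participating UWV offices, and responsible for disability assessments" under the WIA were asked to take part. Neither the number asked nor the number who agreed is given.
- **Randomization:** "Randomization will be conducted at the individual claimant level", and "To prevent unequal groups, 3 blocks will be created (3 UWV offices"). Physicians know the design "but will not be informed about the allocation of disability claimants".

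The second numbered hypothesis in the Background is that claimant and physician will both be more satisfied with the interaction. The Discussion names patient and physician satisfaction as the outcomes that stand for better communication.

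**The concern.** A two-sample t-test treats every rating as independent. Ratings given by one physician are likely to resemble each other, because each rater has a habitual level on a 10-item Likert form. The same applies to the physician-reported claimant activity and assessment time. Claimants who share a physician may also resemble each other in satisfaction, because they met the same person, although here each rater is different.

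Allocation is by claimant within office, so a physician who sees several participants will usually see both arms. The design thus offers a comparison of arms within physician, from which the rater's level drops out. The planned test does not use it, nor does it use office, the randomisation stratum.

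At stake is precision for one of the trial's two numbered hypotheses. The power calculation covers empowerment only, so no stated power stands behind the satisfaction outcomes.

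**Working it through.** **1. The plan's own figure.** The Sample size section gives SD 0.70, power 0.90, α 0.05, 86 per group, 25% dropout and about 230 in total. The absolute size of the 10% difference is not stated; assume 0.35 (10% of a score of 3.5), which is 0.5 SD.

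- n per arm = 2 × (1.960 + 1.282)² × 0.70² / 0.35² ≈ 84.1, rounded up to 85. The exact two-sided t-test calculation gives 85.03, rounded up to 86.
- 86 / 0.75 = 114.7, so 115 per arm and 230 in total.

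The figure reproduces. The expected number of analysed claimants is 2 × 86 = 172, used below as the number of ratings.

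**2. Is there clustering by physician?** 230 claimants over three offices is about 77 per office. To have one rating per physician, each office would need about 77 participating WIA physicians who each see exactly one study claimant. Repeat ratings are therefore very probable, but this is an inference.

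**3. Type I error of the t-test.** Data were simulated with 172 claimants allocated at random to physicians crossed with arm and no arm effect. One set used 20, 30 or 50 physicians, ICC 0.1 to 0.3 and 4,000 runs per setting. Another used 15, 30 or 60 physicians, ICC 0.05 to 0.3 and 3,000 runs. The t-test rejected in 4.6% to 5.8% of runs in the first set and 4.7% to 5.6% in the second. There is no inflation.

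**4. Variance that could be removed.** Let ρ be the ICC, J the number of physicians and m = 172/J the ratings per physician, taken as equal. With random allocation within physician and ρ known, the variance of the arm difference under a random physician intercept, relative to the t-test, is about

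R = (1 − ρ)(1 + (m − 1)ρ) / (1 + (m − 2)ρ).

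For J = 30, m = 5.73:

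- ρ = 0.1: 0.9 × 1.473 / 1.373 = 0.97
- ρ = 0.2: 0.8 × 1.947 / 1.747 = 0.89
- ρ = 0.3: 0.7 × 2.420 / 2.120 = 0.80

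The first simulation set, in which the number of claimants per physician varies, gave ratios over 20 to 50 physicians of 0.96-0.98, 0.87-0.92 and 0.77-0.83. These are reductions of about 2-4%, 8-13% and 17-23%.

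**5. Power.** With 86 per arm and standardised difference d, power ≈ Φ(z − 1.96), where z = d/√(2/86) for the t-test and z is divided by √R for the mixed model.

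| d | ICC | t-test | Mixed model, J = 30 (formula) | Simulated gain |
|---|---|---|---|---|
| 0.4 | 0.1 | 74.6% | 76.1% | 0-1 points (J = 20-50) |
| 0.4 | 0.2 | 74.6% | 79.3% | 3-5 points (J = 20-50) |
| 0.4 | 0.3 | 74.6% | 83.5% | 7-10 points (J = 20-50) |
| 0.5 | 0.1 | 90.6% | 91.6% | 1.0 point (90.7 to 91.7%, J = 30) |
| 0.5 | 0.2 | 90.6% | 93.5% | 3 points (90.9 to 93.9%, J = 30) |
| 0.5 | 0.3 | 90.6% | 95.6% | 4 points (91.7 to 95.8%, J = 30) |

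Formula and simulation agree within about a point. The standard error of one simulated power near 75% with 4,000 runs is √(0.75 × 0.25 / 4000) = 0.7 points. At ICC 0.05 with 30 physicians, simulated power at d = 0.5 was 91.0% for the t-test and 90.8% for the mixed model, so there is no gain.

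The simulations contain no office effect. Any gain from adjusting for office would be additional and cannot be sized from the article.

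**The case against.** The strongest reply is that nothing here is wrong. Under individual randomisation the t-test is valid, the outcomes are secondary, and another valid analysis is merely more efficient under assumptions that the article does not supply. A one-paragraph analysis section also commonly leaves adjustment terms to the analysis plan. The first part stands and sets the weight of the point. The second does not dispose of it, because the article names the t-test for these outcomes.

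Four limits also stand.

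- The article nowhere says that a physician rates several claimants, and cluster size drives the gain. With 50 physicians the average is only 172/50 = 3.4 ratings each.
- No ICC is given. At 0.1 or below the gain is close to zero.
- The article states no target effect for satisfaction. At d = 0.5, which matches the empowerment calculation under the assumed difference, the t-test already has about 90% power and the gain is smaller than at d = 0.4.
- The argument from rater habit applies to what physicians report. For claimant satisfaction only shared physician quality clusters the ratings, so a high ICC is less plausible.

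A reader might go further and infer that ignoring the clustering makes the t-test anti-conservative, as it would in a cluster-randomised trial. The Randomization section rules that out: claimants, not physicians, are allocated, physicians are crossed with arm, and the simulated error rate stays near 5%. Nor does the article support a definite statement that power is lost, since the ICC and the number of physicians are unknown.

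**Conclusion.** The point holds as a conditional gain in precision. The planned t-tests are valid, but they leave physician and office variation in the error for the two outcomes behind the second hypothesis. Given 172 ratings and 20 to 50 physicians, the removable share of the variance runs from negligible (ICC 0.1 or below) to about a fifth (ICC 0.3). The direction is well supported by the design. The size rests entirely on assumed values for the ICC, the number of physicians and the effect. The case is stronger for physician-reported outcomes than for claimant satisfaction. The primary analysis and the sample size are unaffected.

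**What to change.** In the Statistical analysis section:

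- For physician satisfaction and the physician-reported claimant activity and assessment time, replace the t-test with a linear mixed model: arm and office as fixed effects, physician as random intercept.
- For claimant satisfaction, use the same model where the assessing physician is recorded; otherwise compare arms with adjustment for office. Expect a smaller gain here.

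The cost is slightly more analysis work and a link between each claimant and the assessing physician. For physician questionnaires that link should already exist, since they are e-mailed to the physician after the assessment. For claimant satisfaction the article does not say that the assessor is recorded for every claimant, so this should be confirmed. No extra participants, visits or questionnaires are needed. If the ICC turns out low, the model will give nearly the same answer as the t-test.

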#### Claimants expectation

Questions concerning expectations of claimants on the outcomes of their disability assessment will be asked at T_0_, T_1 _en T_2_. Subjects will be asked whether they expect to receive a disability benefit after the disability assessment (yes/partly/no) and the reason for this belief.

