## Discussion

In many countries, workers with long-term sickness absence can claim a disability benefit. For these patients, the assessment of their disability claim is an important life event and outcomes of these assessments determine important aspects in a patients' life, such as financial certainty and future work status. Although stakes are high for the involved claimant, the general idea is that these patients are passive, not only during the consultation visit with the physician who assesses their disability, but also when searching for possibilities in order to return to work. This attitude will not only complicate the physician-patient relationship, but also aggravate claimants return to work perspectives. Therefore, in the present study we developed the interactive website http://www.wiagesprek.nl.

We applied the IM protocol in the development of this intervention [44]. This protocol proved to be a useful tool for tertiary prevention in occupational health, because it combines a theory-, evidence- and practise-based approach [55]. With the help of the IM protocol important stakeholders, such as claimants and insurance physicians, are involved in the development of the website and definition of learning objectives. For this reason it is hypothesized that the applicability and compliance of these stakeholders will be enhanced.

The aim of the interactive website will be to prepare and empower patients prior to their disability assessment. First, based on existing evidence in other fields of research [56], we hypothesize that empowerment of disability claimants will lead to improvement of the physician-patient communication, operationalized by the outcomes patient satisfaction and physician satisfaction. Improved communication will lead to a better information provision by the claimant which, at its turn, can lead to a more accurate assessment by the physician [57]. Second, empowerment may lead to more knowledge about social security arrangements and disability assessment procedures that will influence claimants' expectations on the outcomes of their disability assessment. Consequently, realistic expectations will have an effect on the perceived justice that claimants experience during the process of determination of their disability benefit. Although not the study's primary objective, we furthermore hypothesize that empowerment of disability claimants may lead to an increased return to work status.

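### Perceived justice and satisfaction get unadjusted t-tests; prespecified models with baseline covariates and UWV office could be more precise, though the t-tests are valid

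*Protocol article*

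**What the plan says.** The Statistical analysis section separates outcomes by how often they are measured. Repeated outcomes are analysed from baseline to follow-up. For the rest: "With data that will be measured on one occasion (e.g. claimant satisfaction, insurance physicians satisfaction and perceived justice) we will use t-tests". In Table 1, claimant and physician satisfaction appear only at T2 and perceived justice only at T3.

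Other sections show what is known before allocation:

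- **Claimants expectation** (asked at T0, T1 and T2): "Subjects will be asked whether they expect to receive a disability benefit after the disability assessment (yes/partly/no) and the reason for this belief".
- **Table 1, footnote:** all six VrijBaan subscales are taken at T0.
- **Study procedures** (text with Figure 1): "When subjects finish filling out the baseline questionnaire, they will be randomized in either the intervention group or control group". Every randomised claimant should therefore have T0 data.
- **Randomization:** "To prevent unequal groups, 3 blocks will be created (3 UWV offices").

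The Discussion gives the reasoning behind the outcomes. For justice: "Consequently, realistic expectations will have an effect on the perceived justice that claimants experience". For satisfaction: "empowerment of disability claimants will lead to improvement of the physician-patient communication, operationalized by the outcomes patient satisfaction and physician satisfaction".

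**The concern.** Satisfaction and perceived justice have no baseline value of their own, so they receive no baseline adjustment, while the repeated outcomes do. Yet variables that may predict them are recorded before randomisation, and office is built into the allocation. A two-group t-test leaves any variance these factors explain in the error term.

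This bears on the second hypothesis in the Background, which concerns claimant and physician satisfaction, and on perceived justice. The Sample size section plans only for empowerment, so precision for these outcomes is whatever that sample happens to give. The plan also tests baseline differences between the groups. If no covariates are named in advance, those tests could prompt adjustment chosen after seeing the imbalance.

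**Working it through.** **1. The plan's own figure.** Inputs from Sample size: SD 0.70, a 10% difference, power 0.90, α 0.05, 86 per group, 25% drop-out. The reference mean is not stated. I assume about 3.5, so the difference is 0.35, or 0.5 SD.

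- n per group = 2 × (1.960 + 1.282)² × 0.70² / 0.35² = 84.1, rounded up to 85. The t-based calculation gives 85.03, rounded up to 86, as stated.
- Total = 172 / 0.75 = 229.3, rounded up to 230, as stated.

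No SD, R² or power is given for justice or satisfaction. I therefore use 172 analysed claimants (86 per arm) and an assumed range of R².

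**2. Gain before any cost.** SE ratio = √(1 − R²). Equivalent unadjusted N = 172 / (1 − R²). Power is a two-sided normal approximation at α 0.05 for illustrative differences of 0.4 and 0.5 SD.

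| R² | Fall in SE | Equivalent N | Power, 0.4 SD | Power, 0.5 SD |
|---|---|---|---|---|
| 0 | 0% | 172 | 0.746 | 0.906 |
| 0.05 | 2.5% | 181 | 0.768 | 0.920 |
| 0.10 | 5.1% | 191 | 0.790 | 0.933 |
| 0.20 | 10.6% | 215 | 0.835 | 0.956 |

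**3. Cost of estimating covariates.** With q covariate terms, the expected SE ratio is √[(1 − R²) × 169 / (169 − q)], where 169 = 172 − 3. Here R² refers to all covariates together. The net gain is zero at R² = q / 169.

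| Model | q | R² = 0 | R² = 0.05 | R² = 0.10 | R² = 0.20 | Break-even R² |
|---|---|---|---|---|---|---|
| Office (2) + expectation (2) | 4 | 1.012 | 0.986 | 0.960 | 0.905 | 0.024 |
| Office (2) + one empowerment score (1) | 3 | 1.009 | 0.983 | 0.957 | 0.902 | 0.018 |
| Office (2) + all six subscales (6) | 8 | 1.025 | 0.999 | 0.972 | 0.916 | 0.047 |

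The short models cost about 1%. Entering all six subscales would remove almost the whole gain at R² = 0.05.

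**4. Validity check by simulation.** There were 6,000 runs per setting with 86 per arm and a three-category covariate split 50/30/20% (assumed), without an office factor. Across R² from 0 to 0.30, type I error was between 4.6% and 5.1%, adjusted or not. At 0.4 SD the t-test's power was about 0.74. Adjusted power was 0.731 at R² = 0 (t-test in the same runs 0.741), then 0.755, 0.780 and 0.828 at R² = 0.05, 0.10 and 0.20. This agrees with the formulas, including the small loss when the covariate predicts nothing.

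**The case against.** The strongest reply is that nothing here is wrong. Under individual randomisation the unadjusted comparison is unbiased with correct type I error, these are secondary outcomes without a power target, and the stated method contradicts nothing else in the article. That stands, and it limits the point to efficiency.

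Three stronger readings are tempting, and the article does not support them.

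- **That the protocol makes the T0 answer a driver of perceived justice.** The Discussion speaks of realistic expectations, formed after empowerment and knowledge have acted. The T0 item records only whether a benefit is expected, not whether that is realistic. Its relation to justice at T3 may depend on the decision, which claimants learn at about that time. Its value as a predictor is an assumption.
- **That expectation belongs in the satisfaction models.** The Discussion routes satisfaction through empowerment and communication. T0 empowerment is the baseline variable that this path points to.
- **That precision is certainly being lost.** R² is not given and could be near zero, where adjustment costs slightly more than it returns. The illustrative effect also matters: at 0.5 SD, R² = 0.20 raises power only from 0.906 to 0.956.

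It can also be said that a condensed article leaves adjusted models to the analysis plan. That carries less weight here, because the article does not leave the method open: it names the t-test.

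**Conclusion.** The point holds as a modest, low-cost improvement to a method the article states. The t-tests are valid. Prespecified adjustment would probably help if the T0 variables or office predict these outcomes, and would do slight harm if they do not. Net of the cost of estimation, the short models change the standard error by between about +1% (R² = 0) and −10% (R² = 0.20).

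This rests on 86 analysed claimants per arm, which the plan sets for empowerment and not for these outcomes, and on an assumed R². Naming the covariates in advance also removes the temptation to choose them from the planned baseline tests, whatever R² turns out to be.

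**What to change.** Replace the t-tests for these outcomes with linear models specified before the data are analysed:

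- **Perceived justice (distributive and procedural, separately):** arm, UWV office and T0 expected benefit in its three categories.
- **Claimant satisfaction and physician satisfaction:** arm, UWV office and one T0 empowerment score, defined in advance. The article defines no total score, so the chosen score must be named; the six subscales should not all be entered.

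Use these covariates whatever the observed baseline imbalance, and report the unadjusted difference beside the adjusted one. Do not adjust for expectation at T1 or T2: the website may change it, and adjusting would remove part of the effect under study.

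The cost is a few sentences in the analysis plan and three or four degrees of freedom per model. No new data are needed.

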### Study groups

All participants will be able to access the homepage of the website http://www.wiagesprek.nl. From this homepage, participants from the intervention group can enter the Internet intervention with a username and password. These will be sent to participants after they have filled out an online application form. Comparably, participants from the control group will be directed to a website with commonly available information only. This control group website will only contain brief information about disability assessment procedures, which can normally be found in standard UWV brochures.

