### Process evaluation

Among the participants of the intervention group, experiences with the use of the intervention will be evaluated. This evaluation will be assessed with a brief questionnaire at T_3_. This questionnaire contains both quantitative (e.g. a generic grade for the website) and qualitative questions (e.g. "Do you have any suggestions to improve the website?"). Reasons for complying or not complying will be asked in this questionnaire as well, in order to obtain insight into the potential success of implementation.

Furthermore, the website http://www.wiagesprek.nl will automatically collect data on website usage, so that we can determine compliance and which components are most frequently used. All actions on the website of each claimant will be tracked and stored in a database.

After finishing the research, we will interview five claimants and five insurance physicians, who assessed disability of study participants, on their experiences with the intervention.

For an overview of measurements, see table 1.

**Table 1 T1:** Schedule of measurements

Outcome measure	T_0_: 2 weeks prior to disability assessment	T_1_: Prior to disability assessment	T_2_: After disability assessment	T_3_: 6 weeks after disability assessment	T_4_: 4 months after disability assessment
*Empowerment**	X	X			X

*Claimants satisfaction*			X		

*Perceived Justice*				X	

*Subjective knowledge*	X	X			

*Claimants expectations*	X	X	X		

*Coping Strategy*	X	X			

*Perceived Work Ability*	X	X			X

*Claimants preparation*		X			

*Return to Work*					X

*Process Evaluation*				X	

*Physicians satisfaction*			X		

* The following subscales from the VrijBaan empowerment questionnaire are included in the questionnaire:

T_0_: all subscales

T_1_: subscale Competence and Impact

T_4_: all subscales

NB: The Pearlin Mastery Scale and the General Self-efficacy scale can be distracted from the T_0_, T_1 _and T_4 _measurement

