To our knowledge, this is the first study in the field of disability management that focuses on an eHealth approach aiming at empowerment of patients, which contributes to a more active participation of claimants in the disability assessment. One of the main strengths of this pragmatic trial is that it uses an innovative method that is easily accessible by a relatively high number of claimants in the Netherlands at a low cost. Once proven effective, this will make chances of a nationwide implementation high.

We choose the Internet as the method to deliver the intervention, based on evidence regarding the effectiveness of online interventions on behavioural change outcomes in general [42], and more specifically, on patient empowerment [58,59]. Also, literature suggests that there are many advantages of using the Internet to deliver health care interventions. These advantages include the unique characteristics of Internet technology (e.g. the use of video transmission techniques), its cost-effectiveness, the possibility to reach isolated or stigmatized groups, the timeliness and easy access of information or advice, and the flexibility of user control of the intervention [60]. However, there are also disadvantages of using the Internet to deliver health care interventions. A disadvantage of web-based interventions which also may play a role in the present study, is that compliance in web-based interventions is sometimes low [42]. However, by adapting the intervention to the specific needs of the stakeholders (as was conducted by using the IM protocol) we expect to reduce the risk of low compliance in this intervention.

From a research perspective, the results and process evaluation of the current study will give insight in methods to enhance patient-physician communication as well as insight in the effectiveness of online tools to increase patients' participation in the patient-physician encounter.

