There are also some limitations. The most important limitation is that this study may possibly suffer from selection bias. Results from our pilot study showed that probably a large proportion of the claimants we will approach, will not participate in the study. If characteristics from these non-participants differ substantially from participants, the validity and applicability of the study results will be threatened [61]. In a trial aiming at empowerment this especially may play an important role, because of the expected higher response among more empowered claimants than among those who are less empowered. We therefore hope that a proper non-response analysis will point out that the results are not restricted to a selected population.

Results of the *Empowerment *study will be available in late 2010. If the results are positive, the website http://www.wiagesprek.nl may be implemented nationwide after possible adjustments on basis of the study's conducted process evaluation.

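### A per-protocol comparison based on website use would select essentially in one arm and lose the protection of randomisation; a complier-average effect answers the same question better

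*Protocol article*

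**What the plan says.** The Statistical analysis section sets the primary comparison: "The primary analysis will be a comparison of the change in empowerment between the intervention and control group following the 'intention-to-treat' principle". It closes the paragraph with "Additionally, a per-protocol analysis will be performed". That sentence names no population, no threshold of use and no treatment of controls.

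Elsewhere the article describes what there is to comply with:

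- **Intervention arm.** Participants are asked to complete five self-paced modules (Description of the intervention). They enter the site with a personal username and password (Study groups).
- **Control arm.** "This control group website will only contain brief information about disability assessment procedures" (Study groups). No modules, task or login are described.
- **Usage log.** The intervention site "will automatically collect data on website usage, so that we can determine compliance and which components are most frequently used" (Process evaluation).
- **Self-report.** "Among the participants of the intervention group, experiences with the use of the intervention will be evaluated" at T3, and that same questionnaire asks for reasons for complying or not.
- **Both arms.** At T1 all claimants are asked how they prepared and which websites they visited (Claimants preparation).

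**The concern.** Compliance as described here means using the intervention site. If the per-protocol set is built on it, non-users leave the intervention arm, while the controls who would also not have used the site cannot be identified and stay in. The two groups are then no longer randomised counterparts. Any tendency of users to change more, or less, than non-users for reasons unrelated to the website enters the estimate as if it were an effect.

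This matters most if the intention-to-treat result is null and website use was modest. A positive per-protocol result could then be read as showing that the site works for those who use it. The Discussion foresees nationwide implementation if results are positive, so that reading would carry weight. The problem lies in the comparison itself; it is more than a missing definition that an analysis plan might supply.

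**Working it through.** **Inputs from the Sample size section.** SD 0.70 per subscale, 86 per group, power 0.90, α = 0.05, 25% dropout, about 230 in total. The absolute difference behind the 10% is not given.

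**The plan's own figures.** The difference detectable with 86 per group is 0.70 × √(2/86) × (1.960 + 1.282) = 0.346, or about 0.35 points (0.5 SD). With 0.35, a two-sided t-test needs 86 per group (power 0.903). Dropout: 172/(1 − 0.25) = 229.3, rounded up to 230. Both stated figures reproduce.

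**Assumptions not in the document.** Let *c* be the proportion of the intervention arm that uses the site. Let *δ* be the amount, in SD units, by which users would do better than non-users without any website effect. The true effect is zero, 86 are analysed per arm before selection, and all controls are kept.

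**Bias.** The whole-arm mean is *c* × users + (1 − *c*) × non-users, so users exceed it by (1 − *c*)*δ*. Controls sit at the whole-arm mean, so this is the bias.

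**False-positive rate.** In SD units, SE = √(1/(86*c*) + 1/86). The two-sided rate is Φ(−1.96 + bias/SE) + Φ(−1.96 − bias/SE). For *c* = 0.5 and *δ* = 0.3: bias 0.15, SE = √(1/43 + 1/86) = 0.187, ratio 0.803, rate = Φ(−1.157) + Φ(−2.763) = 0.124 + 0.003 = 0.127.

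| Use *c* | *δ* (SD) | Bias (SD) | Bias (points, × 0.70) | Share of 0.35 | False-positive rate |
|---|---|---|---|---|---|
| 0.5 | 0.1 | 0.05 | 0.035 | 10% | 5.8% |
| 0.8 | 0.3 | 0.06 | 0.042 | 12% | 6.6% |
| 0.5 | 0.3 | 0.15 | 0.105 | 30% | 12.7% |
| 0.5 | 0.5 | 0.25 | 0.175 | 50% | 26.8% |
| 0.3 | 0.5 | 0.35 | 0.245 | 70% | 34.5% |

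The rates depend only on *c*, *δ* and the number analysed. The 0.70 affects only the conversion to points.

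**A second selection model.** Here users are the top fraction *q* of a normal propensity that correlates *ρ* with the outcome. At *q* = 0.5, *ρ* of 0.1 and 0.3 give a bias of 0.06 and 0.17 points and rates of 7% and 26%. At *q* = 0.8 the corresponding values are 0.02 and 0.07 points, and 5.5% and 10%. With *ρ* = 0 there is no bias. With *ρ* = −0.2 the bias runs against the website, from −0.05 points (*q* = 0.80) to −0.15 points (*q* = 0.35).

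**The alternative.** Take a true effect of 0.5 SD in users, *c* = 0.5 and *δ* = 0.3. Per-protocol gives 0.5 + 0.15 = 0.65 SD. The intention-to-treat difference is 0.5 × 0.5 = 0.25 SD, and dividing by *c* recovers 0.50 SD. In simulations of the null cases with 50% use (*δ* 0.3 and 0.5) and 30% use (*δ* 0.5), two-stage least squares rejected in about 4% to 5%. Its SE is about the intention-to-treat SE divided by *c*: √(2/86) = 0.153 SD becomes about 0.305 SD at 50% use.

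**The case against.** The strongest reply is that one sentence in a journal article fixes no population. Its definition may properly sit in a full protocol or analysis plan that is not shown. Several stronger readings are tempting, and the document does not support them:

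- **That selection is possible only in the website arm and every control is kept.** No section says so. The T1 questions could exclude controls for contamination, and either arm could lose claimants for eligibility breaches or missing questionnaires. The statement "All actions on the website of each claimant will be tracked and stored in a database" leaves open whether control use is logged. Exclusions resting only on pre-randomisation eligibility would leave the comparison randomised.
- **That the protocol predicts users to be more empowered than non-users.** The "expected higher response among more empowered claimants than among those who are less empowered" in the Discussion concerns joining the study, not using the site after randomisation.
- **That the protocol expects low use.** It says that "compliance in web-based interventions is sometimes low" and that this may play a role here. It then says that tailoring the site to stakeholders is expected to reduce the risk.
- **That the bias must favour the website.** The primary outcome is change, so a stable difference in level cancels. Ceiling effects, regression to the mean or heavier use by worried claimants could reverse the sign.

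It is also fair to say that the analysis is supplementary, and that a complier-average estimate needs its own untestable assumption. Its null test is essentially the intention-to-treat test.

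These points limit the wording and the certainty about direction. They do not remove the core. Excluding contaminated controls does not identify the controls who would have used the modules, so users still lack their randomised counterparts. Change scores do not remove differences in motivation that drive change. Satisfaction and perceived justice are measured once and compared by t-test; if the per-protocol analysis extends to them, no baseline value offsets a difference in level.

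**Conclusion.** The point holds in a limited form. Since the only compliance the article describes is use of the intervention site, a use-based per-protocol set would select essentially in one arm and would not be a randomised comparison. A bias towards the website is the more plausible direction but is not established.

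The size cannot be fixed from the document. Under the assumptions shown, at 50% use with users 0.3 to 0.5 SD better, it is 0.105 to 0.175 points, with a false-positive rate of about 13% to 27% instead of 5%. With high use or a small user difference it is minor (about 6% to 7%). The intention-to-treat primary analysis, the sample size and the power are untouched. This is a cheap improvement to a supplementary analysis and does not threaten the trial's main conclusion.

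**What to change.** For the question of effect among users, replace the per-protocol comparison with a complier-average causal effect, or give that effect precedence:

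- Use two-stage least squares with randomised arm as the instrument and logged use of the intervention site as the exposure.
- Take any login as the main threshold, so that no effect in non-users is plausible, and fix it before outcomes are seen. Report number of modules completed as a sensitivity analysis.
- Adjust for baseline empowerment (where measured) and UWV office.
- Analyse claimants with outcome data, with the same missing-data handling as the intention-to-treat analysis.
- If a per-protocol table is kept, label it descriptive and non-randomised.

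The cost is a change of wording and one extra model on data already planned for collection. The downsides should be stated: a wider confidence interval (about double the intention-to-treat standard error at 50% use), an explicit exclusion assumption, and no evidence against the null beyond the intention-to-treat test.
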